## Introduction

The performance of a 12-lead ECG is recommended in the assessment of patients with suspected acute coronary syndrome (ACS) presenting in the community to emergency medical services (EMS).^1–3^ A prehospital 12-lead ECG (PHECG) informs decision-making in three components of immediate care: targeted prehospital treatment, transport to an appropriate receiving hospital and provision of information required to activate a response from the receiving cardiac catheter laboratory when ST-segment elevation myocardial infarction (STEMI) is suspected.^4^

This study builds on our previous research, which reported an association between PHECG and lower short-term mortality following STEMI and non-STEMI (30-day mortality 7.4% vs 8.2%, OR 0.94, 95% CI 0.91 to 0.96).^5^ Earlier research focused on the association of PHECG with process-of-care quality descriptors such as ‘call-to-reperfusion’ time.^6 7^ A subsequent systematic review and meta-analysis has confirmed the association of PHECG with improved clinical outcomes,^8^ and this evidence has been incorporated into international guidelines and quality indicators for prehospital care of patients with ACS.^2 3^ However, we found PHECG was underused, particularly in older patients, women and people with comorbidities.^5^

We showed that women were less likely to receive PHECG than men (OR 0.87, 95% CI 0.86 to 0.89),^5^ and suggested that this may be because the majority of EMS personnel at that time were male. The lower rate of PHECG in women was also reported from the national SWEDEHEART (The Swedish Web-system for Enhancement and Development of Evidence-based care in Heart disease Evaluated According to Recommended Therapies) registry (OR 0.89, 95% CI 0.87 to 0.92),^9^ though these authors offered a different explanation related to ‘uncontrolled confounding of presenting symptoms and type of myocardial infarction’. A systematic review reported that women are less likely to present with chest pain and more likely to have prior heart failure, which may ‘mask’ the true diagnosis.^10^

Emergency situations force clinicians into a reliance on past experiences,^11 12^ intuition and personal decision rules (‘rules of thumb’),^13^ even though these approaches are potential sources of error and bias.^14^ In prehospital emergency care, suggested influences on clinical decisions include a desire to ‘cover one’s back’,^15^ pragmatism (busy shift or end of a shift)^16^ and multilevel system influences.^17^

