### Estimated sample size

WP1: all eligible patients in MINAP will be included in analysis. Formal power calculations are therefore unnecessary, but we anticipate that data extraction and linkage will generate a dataset comprising over 500 000 cases.

WP2: we will sample 1650 cases at random from the MINAP database using a stratified sampling method. We will oversample by 10% (165 cases) to allow for any cases where the corresponding EMS clinical records cannot be located. Based on information received from NICOR, we expect approximately a 2:1 ratio of PHECG cases to non-PHECG cases (NICOR, personal communication). Assuming this, we will have 80% power (using 5% significance) in detecting a standardised statistical effect of 0.15.

WP3: six EMS clinician focus groups (two per EMS), each comprising up to eight participants, will be convened, purposively sampling to capture the views of staff in both urban and rural settings within large EMS. We aim to obtain depth with a sample size that is neither too small to contain various aspects of the phenomenon nor too large to allow depth of analysis in this qualitative study.^23^

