### Data collection

WP1: we will use existing MINAP registry data, collected prospectively at each hospital using a secure electronic system, encrypted and transferred online to a central database in which patient identity is protected.^21^ We will link MINAP data to ONS Civil Registry mortality data at individual level through NHS Digital.

WP2: we will randomly select a cohort of patients with and without PHECG, with ACS recorded in MINAP, for the three participating EMS using a unique identifier for patients in MINAP who came to hospital via EMS. The sample will be stratified by preagreed demographic variables (such as sex and age band) to ensure it is sufficiently representative. We will report key characteristics of the sample, those of the MINAP ACS subpopulation (those who came via EMS), and the overall MINAP population.

We will employ and train paramedic researchers at each site to retrieve and extract data from the EMS records of each sampled patient. We will collect data on factors that may influence the use of a PHECG which are not recorded in MINAP, including coded data on patient symptoms, prehospital diagnosis of ACS, EMS clinician training level and sex, patient refusal, patient ethnicity, language spoken, capacity to communicate and/or consent. The paramedic researchers will extract relevant narrative data from the ‘free-text’ section within EMS records. A second researcher will independently extract data for a random sample of 10% of the cases for quality assurance purposes.

WP3—we will conduct focus groups using a semistructured approach, aiming to explore the views of EMS clinicians about the role of PHECG, experiences of assessing patients with STEMI and non-STEMI, and influences on whether or not to record a PHECG. A topic guide will be constructed in the context of the quantitative findings and with input from EMS clinicians, patient and public representatives, and in the context of literature that highlights complexity and multiple influences on decisions made in the EMS setting. Focus group discussions will be digitally recorded and transcribed verbatim. Participants will be briefed at recruitment and at the beginning of each focus group not to disclose any information that might serve to identify individual(s).

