### Analysis

WP1—available demographic data will be presented using interval categories for continuous variables where appropriate. We will present mortality as (1) the proportion occurring within 30 days of hospitalisation, and (2) time to death, summarised using Kaplan-Meier survival curves. We will estimate (with 95% CIs) the outcomes associated with the performance of PHECG via a binary variable, adjusting for other statistically significant demographic and clinical variables.

A similar modelling approach will be used for other categorical variables of interest (for instance, use of reperfusion); natural extensions within the framework of generalised linear models will cover both the analysis of any counts and measurement outcomes of interest.

WP2—partitioning our sample of ACS cases by PHECG or not, we will use univariate and multivariate analyses to explore differences in patient symptoms and other factors between these two groups; we will report and explore differences across stratifying variables (such as age band, sex), and across categorisations emerging from consideration of free-text narratives in EMS records). We will use binary logistic regression to explore the extent to which factors are associated with PHECG use or not in ACS cases, reporting odds ratios (with 95% CIs) for statistically significant variables. Inter-rater reliability of data retrieval will be assessed using Cohen’s kappa.

WP3—focus group transcripts will be managed using NVivo software.^24^ Initially, we will conduct an inductive thematic analysis, using bracketing, and with iteration to the coding framework based on deep reading of the data, discussion within the research team and member checking. We will then use framework analysis^23^ and analyse whether the generated themes show consensus or dissent when considered against any differences in the characteristics of the focus group participants (eg, grade of EMS clinician, local practice). At least two researchers will read, reread and draft a coding framework for discussion and blinded application to at least two transcripts. The coding framework will be developed iteratively by discussion throughout the analysis process. Researchers involved in the qualitative data collection and analysis will meet regularly to reflect on their assumptions, personal influences and data interpretations.

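### WP2 filters its regression odds ratios by statistical significance, which omits imprecise estimates and exaggerates the ones shown

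*Protocol article*

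**What the plan says.** Under Analysis, the WP2 paragraph of the protocol article first describes univariate and multivariate comparisons of cases with and without a PHECG, and says "we will report and explore differences across stratifying variables (such as age band, sex"), with no significance condition attached. It then turns to binary logistic regression for the association of factors with PHECG use, and ends with "reporting odds ratios (with 95% CIs) for statistically significant variables".

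Under Estimated sample size, "we will sample 1650 cases at random from the MINAP database", with a further 165 drawn to cover records that cannot be found. The authors state that "we expect approximately a 2:1 ratio of PHECG cases to non-PHECG cases" and that "we will have 80% power (using 5% significance) in detecting a standardised statistical effect of 0.15".

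The Introduction assigns to WP2 the research question on social, demographic and presenting differences. It also gives the group's earlier sex effect: "women were less likely to receive PHECG than men (OR 0.87, 95% CI 0.86 to 0.89").

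**The concern.** The regression ORs are the adjusted answer to the WP2 research question, and WP4 draws on WP2 when it informs an intervention. A rule that shows an estimate only if it is significant has three effects.

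- **Omission.** A factor with a real but modest association, or one that is uncommon in the sample, usually drops out. Without its interval, nobody can see whether the data argue against an association or say very little.
- **Exaggeration.** With limited power, only estimates that happen to be large pass the filter, so those shown are on average too far from 1.
- **Chance findings.** When many factors are tested and only the significant ORs appear, it is hard to judge how many of them are chance results.

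The rule bites hardest on what WP2 was set up to collect because the MINAP registry lacks it: symptoms, clinician training level and sex, ethnicity, language, and capacity to communicate or consent.

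**Working it through.** **1. The plan's own power figure.** Inputs from Estimated sample size: 1650 cases at 2:1 (1100 and 550), standardised effect 0.15, 5% significance. Sidedness is not stated; two-sided is used.

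- SE = √(1/550 + 1/1100) = 0.0522
- 0.15 / 0.0522 = 2.872
- Power = Φ(2.872 − 1.960) = 81.9%

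The stated 80% is reproduced.

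**2. The design effect beside the earlier sex effect.** The article does not say what kind of variable the 0.15 refers to. Under the usual logistic conversion, log OR = d × π/√3:

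- d = 0.15 gives an OR of exp(0.272) = 1.31, or 0.76 in the other direction.
- OR 0.87 gives |d| = 0.139 × √3/π = 0.077, about half the design effect.

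**3. Power for the regression OR for sex.** Inputs: OR 0.87 (Introduction) taken as the true effect; N = 1650; PHECG use 2/3 overall; unadjusted model; 5% two-sided threshold. The share of women is not in the article, so 35% is assumed, with a range of 30% to 50%.

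At 35% women (577.5 women, 1072.5 men), an overall rate of 2/3 with OR 0.87 needs PHECG rates of 0.678 in men and 0.646 in women.

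- SE(log OR) = √[1/(1072.5 × 0.678 × 0.322) + 1/(577.5 × 0.646 × 0.354)] = 0.109
- |log 0.87| / SE = 0.1393 / 0.1088 = 1.280
- Power = Φ(1.280 − 1.960) + Φ(−1.280 − 1.960) ≈ 25%
- Largest observed OR below 1 that reaches significance: exp(−1.96 × 0.1088) = 0.81

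**4. Size of the estimate when it is shown.** The mean z-value given significance in the true direction is 1.280 + φ(0.680)/Φ(−0.680) = 1.280 + 0.3166/0.2483 = 2.555. The ratio to the truth is 2.555 / 1.280 = 2.0. The average shown OR is exp(−2.555 × 0.1088) = 0.76.

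**5. Sensitivity.**

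| Setting | Power | Inflation of absolute log OR |
|---|---|---|
| 30% women | 23% | 2.06 |
| 35% women | 25% | 2.00 |
| 50% women | 27% | 1.93 |
| 35% women, N = 1485 | 23% | 2.09 |
| 35% women, N = 1815 | 27% | 1.92 |
| 35% women, true OR 0.86 | 28% | 1.86 |
| 35% women, true OR 0.89 | 19% | 2.34 |

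The Introduction puts recent PHECG use at 64% (STEMI) and 44% (non-STEMI), so overall use below 2/3 is possible. At 50% use, power is 25% to 29% over 30% to 50% women, and inflation is 1.98 to 1.83.

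**6. An uncommon ambulance-record factor.** The article gives no prevalence or expected effect for these factors, so this is a pure what-if. Suppose a binary factor is present in 5% to 10% of cases and its true OR is 0.76, the design-size effect. With 1650 cases at 2:1:

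- At 5%: SE 0.232, power 22%, inflation about 2.2.
- At 10%: SE 0.169, power 36%, inflation about 1.6.

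**The case against.** The strongest reply is that the same paragraph already commits to reporting differences across the stratifying variables and names sex, with no significance condition. Data collection also names sex as an example stratifier and promises key characteristics of the sample. A reader might infer from the power figures that the sex difference would go unreported three times in four. The article does not support that: what could be missing is the regression OR with its interval, not all information on sex. This part of the reply stands. It does not rescue the rule, because the earlier clause promises no OR, interval or adjusted estimate, and it covers stratifiers and categories derived from free text, not most of the ambulance-record factors.

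Further points carry some weight:

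- WP2 was not sized for an OR of 0.87, and sex is already held in MINAP, where WP1 expects over 500 000 cases. Sex is therefore an illustration only, and its figures cannot be carried over to other factors.
- The share of women is assumed, and an OR from an earlier cohort is taken as true. The result hardly moves over plausible shares.
- The clause does not contain the word only, and it gives no threshold. The restriction is nevertheless its natural reading, and 5% is the level used for the sample size.
- WP2 is exploratory, its findings are combined with WP1 and WP3 by discussion, and any intervention is to be tested later in a randomised trial. The main candidate factors are also listed, though not exhaustively. This lowers the severity.

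It is no answer that a fuller plan may say more. The fault is a rule the article states, not a detail it leaves out.

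**Conclusion.** The concern holds for the regression ORs. Followed as written, the rule filters the adjusted WP2 estimates by p-value, biases those shown away from 1, and withholds the intervals that would show how little is known about the rest.

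For sex, with the earlier OR of 0.87 as the truth, 1650 cases, a 2:1 ratio and 30% to 50% women, the OR and its interval would be omitted in about 73% to 77% of repetitions. When shown, the absolute log OR would be about twice its true value. These figures rest on the assumed share of women, an unadjusted model and a 5% two-sided threshold.

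The direction of the problem for the ambulance-record factors does not depend on the sex figures. Its size for them cannot be derived from the article.

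This should be fixed. It does not invalidate WP2, since no primary outcome or treatment decision depends on it.

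**What to change.** Replace the final clause of the WP2 regression sentence with: *Odds ratios with 95% CIs will be reported for every factor examined in the univariable and multivariable models, whatever its p-value.* Add: *Non-significance alone will not be read as absence of association.*

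Do not add a rule that declares no association once the interval excludes the design-size OR of about 1.3. With SE 0.109, an observed OR of 0.87 has an interval of about 0.70 to 1.08. That excludes 1.3, so the earlier sex effect itself could be dismissed. A symmetric version (0.76 to 1.31) fails as well: an observed 0.95 has an interval of about 0.77 to 1.18, which would pass although it is compatible with 0.87.

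The cost is two sentences and a longer results table. No new data or larger sample is needed.

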### Patient and public involvement (PPI)

Patients and public representatives (PPI) have been involved in the study since its inception. They played a significant role in the development of the research questions, understanding their relevance to the problem area, the study proposal and the funding application. PPI colleagues’ involvement will continue through their participation in the study oversight activities, in the interpretation of the study results and subsequently in the dissemination of the findings via their local networks and other appropriate routes.

### Clinical and public health implications

Understanding the clinical and non-clinical factors influencing EMS clinicians’ decisions to record a PHECG will enable us to develop (and later, test in a randomised trial) an intervention with the potential to improve PHECG uptake and patient outcomes following an ACS event. With over 85 000 admissions with acute myocardial infarction recorded in MINAP each year, and millions worldwide, the potential for this research to improve outcomes nationally and internationally is substantial.

### Strengths and limitations of the study

The main limitation of the study is its observational, cross-sectional nature, which prevents us from inferring causal relationships. Retrospective chart review methods, although commonly used in emergency research, are not without shortcomings^22^; for example, they are subject to bias by the data abstractors’ through misinterpretation of chart entries or miscoding of data during data abstraction leading to either random or systematic errors. To minimise the effect of those shortcomings, recommended measures from published methodological standards^22^ have been implemented in the design of WP2.

The main strengths of the study are the very large population included in WP1, and its multifaceted, multicentre approach to understanding barriers and facilitators in performing PHECG.

## Ethics and dissemination

The study has been approved by the London-Hampstead Research Ethics Committee (ref: 18LO1679). For patient data used in WP1 and WP2 without patient consent, we have obtained section 251 support from the Confidentiality Advisory Group (ref: 18CAG0164) issued by the Health Research Authority. Participating EMS sites will conduct the study in compliance with the protocol. The study is overseen by a study management group and steering committee with an independent chair.

Findings from this study will be submitted for publication in peer-reviewed scientific journals. We will also present our findings to members of the public and professional stakeholders at local meetings in the three participating EMS, at internal academic seminars, and at national and international conferences relevant to emergency cardiovascular care.
